### Secondary aims

Describe the completion rates and time to complete assessments of participants in each group.Within the group with cerebral palsy, examine the effects of condition-specific characteristics (type of cerebral palsy, functional levels, and pain) and demographics (age, socio-demographic) on participation.

## Materials and analysis

This study is a two-phase validation and acceptability study. It adopts a mixed-model (between and within-group), mixed method (quantitative, qualitative) design to examine the utility of accommodated cognitive assessment tools for children who use switch or eye-gaze control technologies (Figure 1).

**Figure 1 fig1:**
[figure not shown]
Study design.

For typically developing children, two level counter balanced assignment will occur: (i) switch or eye-gaze control technology accommodated administration, and (ii) standard or adapted administration in the first testing session. Children with cerebral palsy will complete the accommodated assessment tools with their preferred technology, with final recruitment of equal numbers of children who use switch and eye-gaze technologies. Children with cerebral palsy will be matched at a 1:2 rate to typically developing children based on gender, Socio-Economic Indexes for Areas (SEIFA) quartiles and age. Assessment tool order will be randomized to counter potential fatigue. Assessments will be undertaken at a clinical assessment site or as a home visit (Figure 2).

**Figure 2 fig2:**
[figure not shown]
Counter balance design for typically developing children.

### Sample size calculations

With the proposed sample size of 80 typically developing children and 38 children with cerebral palsy the study will have power of 80% at 5% overall significance to identify equivalence between the assessment administration methods for all six cognitive assessments, allowing for a 10% drop out rate in the group with cerebral palsy who may require more than one assessment session. This calculation assumes an acceptable difference between standard and modified administration methods of up to 1.25 standard deviations. This sample size will give the study power to correctly detect statistical equivalence between the administration methods in the presence of up to 0.4 standard deviations of variation between standard and modified administration scores on average, which may arise due to a learning effect from repeated assessments or the unfamiliarity of typically developing children with eye gaze or switch technology. Statistical Package Social Science (SPSS v.25) (Statistical Package Social Science, S.F.W, 2018) Sample Power 3 and R (v 4.1.0) (R Core Team, 2021) were used for the power computation.

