### Primary aims and hypotheses

Aim 1. Examine the psychometric properties (measurement agreement and validity) of accommodated assessment tools by comparing the performance of typically developing children on six cognitive assessment tools administered *via* standardised versus accommodated (switch or eye-gaze control) administration.

*Hypothesis 1-1*: The two types of accommodated instruments (switch or eye-gaze control) will yield standard scores that are not statistically significantly different from standardized administration counterparts.

*Hypothesis 1-2*: Accommodated instruments will demonstrate intraclass correlation indexes of agreement with standard counterparts that would be at least 0.75 (Lee et al., 1989).

*Hypothesis 1-3*: Bland Altman plots will provide further evidence of measurement agreement and test bias, with *a priori* criteria of an acceptable upper 95% confidence limit and lower 95% confidence limit of 1.96 SD of the differences between the methods as equal to or smaller than the normative standard deviation (SD = 15; Bland and Altman, 1986).

Aim 2. Describe and compare the performance and user experience of children with cerebral palsy on six accommodated cognitive assessments administered *via* switch or eye-gaze control technologies.

*Hypothesis 2-1*: Group differences (typically developing, cerebral palsy) in the nomothetic span of test scores computed as within-group bivariate correlation matrices, will not be statistically significant.

*Hypothesis 2-2*: Within the group with cerebral palsy, the access method (switch, eye-gaze) will not result in significant differences in the nomothetic spans of test scores.

*Hypothesis 2-3*: Within the group with cerebral palsy, access method (switch, eye-gaze) will not have a significant effect on user experience as indicated by personal ratings of task difficulty and satisfaction.

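### Aim 1's equivalence margin, ICC floor and limits of agreement are not aligned and can give opposite verdicts on the same tool, and the protocol does not say which decides

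*Protocol article*

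**What the plan says.** Three thresholds bear on whether a tool's accommodated version agrees with its standard version in typically developing children.

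- **ICC (Protocol article, Primary aims and hypotheses, Hypothesis 1-2):** "intraclass correlation indexes of agreement with standard counterparts that would be at least 0.75".
- **Limits of agreement (same section, Hypothesis 1-3):** the Bland-Altman limits are acceptable with "1.96 SD of the differences between the methods as equal to or smaller than the normative standard deviation (SD = 15". The hypothesis presents this as further evidence, but gives it its own a priori criterion.
- **Equivalence margin (Sample size calculations):** "This calculation assumes an acceptable difference between standard and modified administration methods of up to 1.25 standard deviations". Power is claimed "in the presence of up to 0.4 standard deviations of variation between standard and modified administration scores on average". The section does not say whether these are normative SDs, sample SDs or SDs of the paired differences.

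Data processing and analysis then plans equivalence tests with multiplicity control, ICCs and Bland-Altman plots. It does not rank them.

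**The concern.** The three numbers measure different things: a mean shift, a correlation-type index and the spread of individual differences. All three nevertheless feed one question, whether a tool can be used in accommodated form. Put on one scale, they differ widely in strictness. A tool could therefore be reported as agreeing under one threshold and not under another, and the choice of which to emphasise could be made after the results are known.

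The margin matters most. On the normative-SD reading, a shift of 1.25 SD moves an average child from the 50th to about the 10.6th percentile, since Φ(−1.25) = 0.106. The project exists to avoid underestimating children's ability, so that is hard to call an acceptable difference.

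**Working it through.** **Inputs from the protocol:** margin 1.25 SD, true difference up to 0.4 SD, ICC floor 0.75, limits bound 15, normative SD 15, 80 typically developing children, 80% power at 5% overall for six tools.

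**Assumptions:** an even split gives 40 children per access method. The correlation r between administrations is 0.5 to 0.75. The multiplicity method is not named, so I use one-sided 0.05/6 (six tools) or 0.05/12 (six tools by two access methods). The SD of differences is SD × √(2(1−r)), i.e. 1.00 SD at r = 0.5 and 0.707 SD at r = 0.75.

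**1. The stated power.** Two one-sided paired t-tests, margin 1.25, true difference 0.4, SD of differences 1 SD, alpha 0.05/6:
- n = 80: about 100%.
- n = 40: 99.7% per test and 0.997^6 ≈ 98.4% jointly (the joint figure uses unrounded power).

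The 80% is not reproduced. Values near it appear only under other set-ups, such as two independent groups of 80 and 36 at 0.05/6 (79.8% joint).

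**2. ICC against limits of agreement.** Half-width = 1.96 × 15 × √(2(1−ICC)), with sample SD 15 and no bias:
- ICC 0.75: 1.96 × 10.61 = 20.8
- ICC 0.80: 18.6
- ICC 0.85: 16.1
- ICC 0.87: 15.0

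In reverse, the bound of 15 needs an SD of differences of 15/1.96 = 7.65, so ICC = 1 − 7.65²/(2 × 225) = 0.87. Any tool with an ICC from 0.75 to just under 0.87 passes Hypothesis 1-2 and fails Hypothesis 1-3. With sample SDs of 12 to 18, an ICC of 0.75 gives ±16.6 to ±24.9, so the gap does not hinge on an SD of exactly 15.

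At the plan's own shift, 0.4 × 15 = 6 points, keeping both limits within ±15 leaves an SD of differences of (15 − 6)/1.96 = 4.59. That is a consistency ICC of 1 − 4.59²/450 = 0.95. An absolute-agreement ICC, which counts the shift as error, would be (225 − 4.59²/2)/(225 + 6²/2) = 0.88. Both are well above 0.75.

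**3. Margin against limits of agreement.** In normative SDs, 1.25 × 15 = 18.75 points, more than 15. If both limits must lie within ±15, a mean shift of 15 to 18.75 meets the margin and can never pass Hypothesis 1-3. A shift of 18.75 also caps an absolute-agreement ICC at 225/(225 + 18.75²/2) = 0.56.

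If the SD meant is that of the differences, the margin is 1.25 × 7.65 = 9.6 to 1.25 × 10.61 = 13.3 points, below 15.

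**4. Chance that a tool truly biased by 1.0 SD meets a 1.25 SD margin.** This is approximately Φ[(1.25 − 1.0)√n / SD of differences − t]. For n = 80, r = 0.75 and 5%: 0.25 × √80/0.707 = 3.16, less 1.66, giving Φ(1.50) = 93%.

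| n | r | alpha 0.05 | alpha 0.05/12 |
|---|---|---|---|
| 80 | 0.75 | 93% | 68% |
| 80 | 0.5 | 72% | 33% |
| 40 | 0.75 | 71% | 31% |
| 40 | 0.5 | 46% | 13% |

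**5. Power if the margin is capped at 1.0 SD.** True difference 0.4 SD, alpha 0.05/12:
- n = 40: 84% (r = 0.5) to 99% (r = 0.75) per test. Jointly for six independent tests, 35% to 96%.
- n = 80: above 99% per test at both correlations.

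**The case against.** The strongest reply is that criteria of different strictness are not contradictory. The ICC threshold is a floor, Hypothesis 1-3 is described as further evidence, and all three can be met together, for example with an ICC of 0.87 or more and little bias. That stands. A reader might infer that the thresholds exclude one another, and they do not. What remains is that they can disagree on the same tool with no stated rule for that case.

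Second, 18.75 points depends on an SD that the section does not name. This also stands: on the SD-of-differences reading the margin falls below 15 points and that limb drops out. The ICC limb does not depend on it.

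Third, Hypothesis 1-3 can be read as capping only the half-width, which would place no bound on the mean shift. Then a shift of 15 to 18.75 points need not fail it. The wording allows both readings, which is itself something to settle.

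Fourth, a tool shifted by 15 points would still face Hypothesis 1-1 (no significant difference) and the other criteria. So a reader should not infer that such a tool would necessarily be declared valid overall, only that it can meet the margin.

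A precedence rule may exist in a fuller document. That would answer which criterion decides, but not the misalignment of the numbers printed here.

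**Conclusion.** The concern holds in this form: thresholds stated in the protocol are misaligned, can return opposite verdicts on one tool, and carry no stated order of precedence. The firmest part is the ICC range of 0.75 to 0.87, which passes Hypothesis 1-2 and fails Hypothesis 1-3 when the sample SD is 15 and bias is nil.

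The margin part is conditional on normative SD units. On that reading a tool biased by a full SD would usually meet the margin at n = 80 and r = 0.75 (93% at 5%, 68% at 0.05/12). It would do so less often with 40 children or a weaker correlation.

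Two stronger inferences are not supported. The failure to reproduce 80% does not show that figure to be wrong, because the SD basis and alpha split are not given. Nor does the arithmetic justify specific replacements such as a 0.8 SD margin or an ICC floor of 0.87. At n = 40, r = 0.75 and alpha 0.05/12, a 0.8 SD margin has only 78% power per test and about 23% jointly. An ICC of 0.87 matches ±15 only when there is no bias.

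**What to change.** 1. State that the margin is in normative SD units and reduce it to at most 1.0 SD: 15 points, or the same in SD units for scaled scores and z-scores.
2. State that Hypothesis 1-3 requires both limits of agreement, including bias, to lie within ±1 normative SD, and that this criterion decides. This rule is needed even with the smaller margin, because a tool with a shift near 1.0 SD could meet the margin and still have a limit outside the bound.
3. Keep ICC ≥ 0.75 as supportive evidence, not sufficient alone, and say which form of ICC is meant.
4. Rerun the power over a range of correlations, naming the SD, the alpha split, the sample size per comparison, and whether 80% is per test or for all six tools jointly.

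The cost is protocol wording and a new power calculation. No more children are needed at r = 0.75. At r = 0.5, joint power of 35% with 40 per access method would have to be acknowledged. A tool may also fail that would have met the present margin, and the stated power will change.

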### Eligibility criteria

#### Inclusion criteria

Aged 5 years to 15 years 11 monthsReside in Australian Capital Territory or New South Wales, AustraliaComprehend one stage instructions as assessed by completion of dichotomous choice screenA reliable yes/no responseAdequate hearing and vision (adjustments accepted) as assessed with caregiver screening survey and ability to pass the Dichotomous Choice Screening (Van Tubbergen et al., 2008)English as a primary language

#### Exclusion criteria

Changes to medication in past month that could affect cognitive functionKnown seizure activity within the past weekPhotosensitive epilepsyHistory of psychosisAn acute psychiatric/mental health issue of parent/guardianCompletion of any of the included assessment tools in the past 3 monthsHistory of Traumatic Brain InjurySignificant health or behavioural changes within the test–retest period

#### Additional inclusion criteria

##### Children with cerebral palsy

Confirmed diagnosis of cerebral palsyCurrent reliance on and adequate use of switch or eye-gaze control technologiesAble to demonstrate scrolling between screens and making selections using their preferred access method (switch or eye-gaze control technology)

#### Additional exclusion criteria

##### Typically developing children

Impairments in dexterity and/or speech that preclude participation in standardized administrationsPreterm birth/very low birth weight (exclusion if <37 weeks gestation or < 1500gm)Diagnosis of cerebral palsy or other neurodevelopmental conditions that adversely affect developmentUnable to learn to use switch or eye-gaze control technologies with training

### Recruitment

Convenience sampling using a snowball recruitment strategy will be adopted to obtain final samples of 80 typically developing children and 40 children with cerebral palsy, including 20 who use switch access and 20 who use eye gaze technology. Community awareness will be generated through flyers and correspondence with churches, sports clubs, independent/catholic schools, the Home Education Association and the NSW/ACT Cerebral Palsy Register. Personal communication with Cerebral Palsy Alliance staff, community links and campaigns on social media moderated by Cerebral Palsy Alliance will also be used for recruitment.

#### Approach to provision of information to participants and/or consent

Parents and caregivers of participating children will provide informed consent. Assent to participate in the study will always be obtained in person from any child or youth as the active participation of the person is required. Assent information has been accommodated on screen to provide children with cerebral palsy the opportunity to independently provide assent using their switch or eye-gaze control technology to let us know if they want to participate or not. Capacity to comprehend and respond to single step questions will be assessed by completion of dichotomous choice screen. This will provide a clear indication if the participant has a reliable yes/no response. Study information and assent questions will be provided in English at an early primary school level to support comprehension. Whilst it will not be possible to definitively assess comprehension of information, the assent activity will allow the participant to be familiar with the screen, demonstrate their ability to scroll between screens and make selections using their preferred access method (switch or eye-gaze control technology). It will also provide an opportunity for further discussion around what the study involves. Children who provide assent will also require parental/caregiver consent to participate in the study. Children who decline participation in the study during the assent process will discontinue involvement regardless of parental consent. If a child is unable to undertake the assent process, parental/caregiver consent and implicit child assent will be used to guide participant involvement. Implicit assent here refers to behavioural compliance and willingness undertake assessment tasks.

### Assessment procedure

After providing assent and informed consent, participants and their parent/caregiver will be invited to attend a site at Cerebral Palsy Alliance, a state-wide disability organisation. Typically developing children will attend two testing sessions where they will complete standard (paper and pencil) and accommodated administration of the assessments using switch or eye-gaze control technologies (Figure 1). Assessment will be undertaken 2–4 weeks apart and counter-balanced to reduce the impact of potential learning effects. Selection criteria and demographic information that can be obtained over the phone prior to the face-to-face appointment, will be collected. For children with cerebral palsy, condition related information and proficiency in switch and eye-gaze control technology access will also be collected. Included in the face-to-face assessment, participants will be asked to demonstrate that they can count from 1 to 20, complete a dichotomous choice test to ensure they have a reliable yes/no response, and will complete (with parent/carer assistance if necessary) the Wong Baker FACES^®^ Pain Rating Scale Revised (FPS-R; Foundation, 2018). Children with cerebral palsy will demonstrate their ability to scroll between screens and make selections using their preferred access method (switch or eye-gaze control technology).

Participants completing the assessment on eye-gaze control technology will have their scan time individualised based on participant needs, with preference recorded. Assessment will then be undertaken. Administration order of measures will be counterbalanced across participants to adjust for fatigue related affects. Where possible, assessment will be completed in one session with breaks offered as necessary. However, if required, administration will be split across multiple sessions. Administration related information will be captured by the assessor *via* the assessor questionnaire. Following assessment, participants will be asked to complete the Quebec User Evaluation of Satisfaction with Assistive Technology (QUEST; Demers et al., 2000) and the National Aeronautics and Space Administration Task Load Index measure (NASA-TLX; Hart and Staveland, 1988) about their experience of undertaking assessment. Each session will take approximately 2 h (Table 1).

**Table 1 tab1:** Included measures/tasks per participant.

**Measures/tasks**	**Description**

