The measurement agreement and validity of the accommodated assessment tools will be investigated by testing hypotheses of equivalence between scores from the standard administration and scores from the accommodated administration of the assessments. These hypotheses will be tested using paired t-tests for Wilcoxon signed-rank tests if the data is not normally distributed. The significance level for these tests will be adjusted to account for multiplicity and control the overall Type I error rate at 5%. Correlations will be investigated between performances on each of the six assessments for all combinations of access methods, and intraclass correlation coefficients (ICC) will be calculated. For the sample of children without cerebral palsy, the sample size will be sufficient to examine Bland Altman plots for further evidence of measurement agreement and test bias. In addition, we will compare the bivariate correlation matrices with adaptive test scores to examine the nomothetic spans of instruments by comparing coefficients using Fisher’s r to z transformations. Regression models will be investigated to examine between group differences in (i) children with cerebral palsy using switch and eye-gaze control technologies for each of the six assessment tools and for the two user experience measures, and (ii) between typically developing children’s and children with cerebral palsy’s performance using switch and eye-gaze control technologies, across all six assessment tools. Potential confounders and effect modifiers will be investigated for these regression models Associations between test results and secondary outcomes for the children with cerebral palsy will be investigated using chi-squared or Fisher’s exact tests.

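### Session order is counterbalanced but absent from the stated agreement analysis, so an average practice effect widens the limits of agreement and lowers the ICC

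*Protocol article*

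**What the plan says.** Under Materials and analysis (text with Figure 1), typically developing children are assigned in counterbalanced fashion to an access technology and to "standard or adapted administration in the first testing session". Assessment procedure puts the two sittings 2 to 4 weeks apart, "counter-balanced to reduce the impact of potential learning effects". Sample size calculations also expects learning: it allows for "up to 0.4 standard deviations of variation between standard and modified administration scores on average, which may arise due to a learning effect" or from unfamiliarity with the technology.

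Primary aims and hypotheses sets the pass marks. Hypothesis 1-2 asks for an ICC of at least 0.75. Hypothesis 1-3 asks that 1.96 SD of the between-method differences be no larger than the normative SD of 15. Data processing and analysis names paired t-tests or Wilcoxon signed-rank tests, ICCs and "Bland Altman plots for further evidence of measurement agreement and test bias". None of these is said to account for session or order.

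The same section plans regressions of typically developing against cerebral palsy performance. It leaves potential confounders and effect modifiers of those regressions to be explored. Children with cerebral palsy take only the accommodated version.

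**The concern.** The design anticipates learning and assigns order to deal with it, but the analysis does not use that order. Counterbalancing removes a practice effect from the average difference, because it pushes the difference up in one half of the children and down in the other. It does not remove the spread between the two halves. Hypotheses 1-2 and 1-3 are judged on exactly that spread. The sample size text budgets for learning as a shift in the average, which is the component that balance cancels, and leaves the remaining component unaddressed.

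At stake are two of the three primary agreement hypotheses: practice between sittings would be charged to the accommodation. For Hypothesis 1-1, worded as no significant difference, the extra variance works the other way and makes the criterion easier to meet.

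**Working it through.** **Plan's own figure.** The sample size section states "power of 80% at 5% overall significance" for equivalence. It cannot be rebuilt from the stated inputs: a paired equivalence calculation with 80 children, margin 1.25 SD and true difference 0.4 SD gives at least 0.97 for all six tools in every variant tried. That is a separate matter. The figure carries no information on p or on the agreement criteria, so the check below does not depend on it.

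**Inputs.**
- Normative SD 15, variance 225 (Hypothesis 1-3).
- Criteria: 1.96 × SD of differences ≤ 15; ICC ≥ 0.75. Hypothesis 1-3 speaks of confidence limits; it is read here as the limits of agreement themselves.
- Assumed: half of the children in each order, and the same average gain p at the second sitting whichever version comes second.
- Assumed: p from 0 to 0.4 SD (0 to 6 points). The protocol states no practice effect.

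**Formulas.** Let d be the method difference. The raw difference, accommodated minus standard, averages d + p in children who take the accommodated version second and d − p in those who take it first. Its overall mean is d. Being second for one version means being first for the other, so p²/4 is added to each method's variance and p²/4 is taken from their covariance. Hence

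- Var(D) = 2(1 − ICC) × 225 + p²
- observed ICC = (225 × ICC − p²/4) / (225 + p²/4)

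**A tool exactly at the limits criterion.** SD of differences = 15/1.96 = 7.65, variance 58.57, true ICC = 1 − 58.57/450 = 0.870.

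| p | Var(D) | 1.96 × SD | Observed ICC |
|---|---|---|---|
| 0 | 58.57 | 15.0 | 0.870 |
| 0.1 SD (1.5 points) | 60.82 | 15.3 | 0.865 |
| 0.2 SD (3 points) | 67.57 | 16.1 | (195.71 − 2.25)/227.25 = 0.851 |
| 0.4 SD (6 points) | 94.57 | 19.1 | (195.71 − 9)/234 = 0.798 |

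**A tool exactly at the ICC criterion (0.75).** At p = 0.2 SD, (168.75 − 2.25)/227.25 = 0.733. At p = 0.4 SD, (168.75 − 9)/234 = 0.683.

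**A tool with room to spare (true ICC 0.90).** Limits of ±13.2 become ±14.4 at 0.2 SD, still a pass, and ±17.6 at 0.4 SD, a fail.

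**Agreement needed to pass at p = 0.4 SD.** For the ICC criterion the true ICC must be (0.75 × 234 + 9)/225 = 0.82 instead of 0.75. For the limits it must be 1 − (58.57 − 36)/450 = 0.95 instead of 0.87.

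**Simulation (80 children, 4,000 runs).** The mean difference stayed at about 0. With true ICC 0.80 and p = 0.4 SD, the chance that the estimated ICC reaches 0.75 fell from 87% to 35%. Removing order returned the limits to their no-practice width (18.5 instead of 22.0).

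**Typically developing against cerebral palsy.** If order is ignored, the typically developing mean on the accommodated version moves by p/2: 1.5 points at 0.2 SD and 3 points at 0.4 SD. With no true difference, a nominal 5% test then rejects about 8% and 16 to 17% of the time. Correlations between tests hardly move (0.50 to 0.52 at p = 0.4 SD).

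**The case against.** The strongest objection is that no practice effect is documented. A reader might take 0.4 SD as the protocol's own estimate of it. The text does not support that: 0.4 SD is a ceiling on the average difference between methods, unfamiliarity with the technology is offered as a second cause, and a symmetric practice effect cancels from that average anyway. This stands, and is why p is treated as an assumption with a range. It limits the size, not the direction.

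A reader might also see a contradiction between excluding children who took any of the tools in the past 3 months and retesting at 2 to 4 weeks. There is none. The exclusion removes uncontrolled exposure before entry; the retest is a planned, counterbalanced one.

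Nor do the documents show that the cerebral palsy comparisons as a whole are biased. The p/2 shift touches only the regression of mean scores, where confounders are left open and order may yet be included. The net direction of that contrast is also unclear, since children with cerebral palsy must already use their technology adequately while the typically developing children may be new to it. Hypothesis 2-1 compares correlations and is almost unaffected; Hypotheses 2-2 and 2-3 lie within the cerebral palsy group and are unaffected.

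Finally, the article is condensed, and model covariates are often left to an analysis plan. That weighs against the regression part. It does not answer the main part, because the article itself fixes the paired tests and the numerical criteria on the differences. The error is conservative for Hypotheses 1-2 and 1-3: it can fail a sound tool but does not pass a poor one.

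**Conclusion.** The point holds for Hypotheses 1-2 and 1-3. With balanced order, any non-zero average practice effect widens the raw limits of agreement and lowers the raw ICC, while the mean difference stays protected. The size rests on an assumed p: slight at or below 0.1 SD, moderate at 0.2 SD, and at 0.4 SD enough to fail a tool whose true ICC is 0.90 on the limits criterion. It also rests on equal numbers per order and equal practice in both orders. The cerebral palsy part is a secondary note on one regression, conditional on order being left out of it. This should be corrected before analysis; it does not undermine the design.

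**What to change.** State that session (period) is included in the paired comparison for each tool, either through order-adjusted differences or through a mixed model with child as random effect and administration and session as fixed effects. Compute the limits of agreement and the ICC from session-adjusted scores, say that the Hypothesis 1-2 and 1-3 criteria apply to those, and report the unadjusted values alongside. A single session term removes only the average practice effect; variation in practice across ages or access methods would remain in the limits, and the report should say so.

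For the regression of typically developing against cerebral palsy scores, add an indicator for having taken the accommodated version second, or a sensitivity analysis limited to the children who took it first (about 40 if order is balanced).

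Order is already assigned by design, so no new data are needed. The cost is analysis wording and about one degree of freedom per tool.
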